**Study 3: In person open-pilot Relaxation Response Resiliency Program in patients with NF1, NF2 and schwannomatosis ([name], Merker, Plotkin and Park, 2014).** This study evaluated the feasibility, acceptability and preliminary effect of the 3RP-NF in adults with NF1, NF2 and schwannomatosis. Patients presenting to our Neurofibromatosis Clinic who reported stress and difficulties coping to their neurologist were asked to participate in the mind-body study. Those who agreed, met inclusionary/exclusionary criteria and signed the informed consent form were enrolled and asked to complete pre- and post-intervention measures via REDCap, an electronic data system. The 3RP-NF had 8 face-to-face sessions, 90 min/session. **Results:** The intervention had relatively low feasibility, with 32 out of 67 patients approached (48%) signing the informed consent form. The main reason cited for non-participation was burden of travel to the clinic. The intervention was highly acceptable, as evidenced by an 80% completion rate (16/20), and a score of 28.3 (out of 32 maximum score) on a Client Satisfaction Scale. Resiliency, quality of life, depression, stress, anxiety, and mindfulness improved significantly by paired t-tests, with effect sizes ranging from .73 to 1.33. Somatization and daytime sleepiness improved substantially but not significantly, with effect sizes of .54 and .92, respectively and  $p = .06$ . Social support and optimism improved modestly, perhaps due to high baseline scores and a ceiling effect. Exit interviews showed that patients believed the intervention was helpful and that the intervention's feasibility could be improved if delivered via videoconferencing with Skype. **Conclusions:** This study allowed us to show that the 3RP-NF is accepted by patients and has potential for efficacy in improving quality of life, and many psychosocial factors. To increase feasibility, the intervention should be delivered via videoconferencing.

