#### **Study 5: [name], Riklin E, Merker V, Macklin E, Park E, Plotkin SR. Mind body therapy via videoconferencing in patients with neurofibromatosis; An RCT. Neurology, 2016.**

**Overview:** This was a single blind RCT pilot study of the 3RP-NF delivered via videoconferencing with Skype, in adults with NF1, NF2 and schwannomatosis, providing primary preliminary data for this application. The transition from face to face to Skype delivery of the intervention was done to improve feasibility and generalizability of the intervention. Patients were recruited through the CTF outreach via a flyer asking for interest in participation in a stress management study. Patients who met inclusionary and exclusionary criteria, including reports of difficulties coping with stress and NF symptoms at intake, were randomized to the 3RP-NF focused on teaching the elicitation of the relaxation response, adaptive thinking and positive psychology tools, or the Health Enhancement Program for NF attention placebo control (HEP-NF) focused on providing educational information on stress, NF, and lifestyle behaviors such as healthy eating, exercise, and sleep hygiene. Both groups were delivered online via videoconferencing with Skype. Participants were blind to the group assignment (intervention versus control). Participants from both groups received the same amount of support from the interventionist and other group members for the duration of the groups. All participants received a patient manual. Those in the 3RP-NF also received a CD that included mindfulness meditation exercises practiced during the group. Data was collected using the REDCap data management system. Patients in both groups completed homework. **Results:** The first 65 potential participants were screened for participation and 63 entered the study, completed consent, provided baseline and were randomized (32 intervention, 31 control). Of these, 63 completed the intervention (at least 6 sessions attended) and provided post-test data (32 in the 3RP-NF and 31 in the control). Of these, 53 provided 6 months follow up data. The abundance of inquiries, 100% post-test completion rate, and 82.5% 6-month follow-up completion rate indicates excellent feasibility and compliance. Satisfaction with participation in the program was high and similar at both post test and 6 months follow up between the 3RP-NF (4.19 and 3.92 out of 5) and the HEP-NF (4.10 and 3.79 out of 5) groups suggesting high acceptability and usability. The similar scores on satisfaction with both 3RP-NF and HEP-NF also suggest that blinding was maintained both at post test and 6 months follow up. Participants were middle-aged (mean±SD 43±years) and predominantly female (73%), college educated (60%), employed (73%), US-based (90%), and diagnosed with NF1 (71% NF1, 19% NF2, 10% schwannomatosis). There were no significant differences in baseline outcome variables between those randomized to 3RP-NF versus HEP-NF except for Psychological QoL, where patients in the HEP-NF had more impaired scores compared to those in the 3RP-NF ( $P < .05$ ). This is considered a chance finding given the lack of significant baseline difference in the other 7 outcome measures. A mixed methods repeated measures ANOVA following intent to treat principles was employed for the data analyses. For primary (Physical Health QoL and Psychological QoL) and secondary (social relations QoL, environmental QoL, depression, anxiety, pain intensity for those with pain higher than 4, and pain interference for those with pain higher than 4) variables we compared the effect of the 3RP-NF versus HEP-NF on changes from own baseline to post-test, and from post-test to 6 months follow-up times using linear contrast. For primary outcomes, improvement from 3RP-NF from baseline to post test was considered clinically meaningful if the mean improvement was higher than the MCID of 6.25. For primary outcomes, durability was established if there was a less than 6.25 decrease in scores from post-test to follow up. Information on minimal clinically important difference (MCID) for the study variables does not exist in patients with NF. In patients with breast cancer, distribution- and anchor-based methods suggested an MCID of 1 on a 4-20 scale for the physical and psychological domains of the WHOQOL-100^33. Extrapolated to the 0-100 scale used for WHOQOL-BREF subscales, this is equivalent to 6.25 units. This value was used to indicate meaningful change for the primary variables. Patients in the 3RP-NF showed greater improvement in Physical Health QoL (7.69; 95% CI: 0.29-15.10;  $P = .040$ ), Psychological QoL [5.57; 95%

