## II. SPECIFIC AIMS

The present proposal is based on qualitative formative work, an open pilot of the face-to-face 3RP-NF, and a pilot single blinded RCT of the 3RP-NF versus HEP-NF, both delivered via videoconferencing with Skype showing feasibility, acceptability, preliminary efficacy and durability. The objective of the study is to test, within a single blinded fully powered RCT, the efficacy of the 3RP-NF as compared to HEP-NF (attention control) in improving co-primary (physical and psychological quality of life) and secondary (social quality of life, environmental quality of life, depression, anxiety, pain intensity and pain interference) outcomes. **Specific aims:**

- Aim 1:** to determine the efficacy of 3RP-NF in comparison to an active control HLI on the co-primary outcomes: physical health QOL and psychological health QOL among patients with NF1, NF2 and schwannomatosis. Secondary outcomes are: social relationships QoL, environment QoL, depression, anxiety, pain, pain interference, gratitude, optimism, mindfulness, coping, social support, empathy and stress. Assessments will be conducted at baseline, post-intervention (8 weeks, primary time point), 6 and 12 months follow-ups (secondary time points). Both intervention and control are delivered via live video with Zoom.

**Hypotheses:** 3RP-NF will be more efficacious in reducing primary and secondary outcomes at post-intervention, and effects will be maintained at 6 and 12 months follow-ups, compared to HEP-NF.

- Aim 2:** to examine the degree to which treatment-dependent improvements in the primary outcomes are mediated by improvements in depression, anxiety, pain intensity, pain interference, gratitude, optimism, mindfulness, coping, social support, empathy and stress (conceptual mediators) and modified by NF type, age, race/ethnicity, learning disability and education level.

**Hypotheses:** Treatment-dependent improvements in the secondary outcomes depicted in the figure below will mediate benefits from 3RP-NR for the primary outcomes. The moderators NF type, age, and race/ethnicity will be associated with differential benefit from 3RP-NF for the primary outcomes.

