## MIND-BODY SKILLS TRAINING FOR ADULTS WITH NEUROFIBROMATOSIS

Neurofibromatosis clinic at MGH (900 visits/year in 2014) and 2) the Children's Tumor Foundation (CTF). Our IRB approved flyers will be posted in various areas of the hospital and emailed periodically to patients in the NF registry via CTF, which includes local (within the United States) and international (outside of the United States) patients. We have used this method of recruitment successfully in our preliminary clinical trial ([name] PI, funding from CTF). CTF has committed their support to recruitment, should this study be funded, and DoD has allowed for recruitment of patients within and outside of the United States. This method of recruitment is advantageous because it has allowed us to recruit patients from across the U.S. and Canada, thus fostering generalizability of results. We do not anticipate any difficulties recruiting, based on our success with working with this population. However, if difficulties occur, we plan to expand our recruitment to other U.S. NF centers with whom we have collaborations, including Children's Hospital in Boston and Johns Hopkins NF Clinic. We will also be recruiting by posting our study on Partners Clinical Trials.

Recruitment will also occur through the Research Patient Database Registry (RPDR). The RPDR is a centralized clinical data registry that gathers data from various hospital legacy systems and stores it in one place. Researchers access the data using the RPDR online Query Tool. They may query the RPDR data for aggregate totals, and with proper IRB approval, obtain medical record data. The RPDR ensures the security of patient information by controlling and auditing the distribution of patient data within the guidelines of the IRB and with the use of several built-in, automated security measures. To identify potentially eligible patients:

- 1) A RPDR query will be performed to identify those patients with chronic pain diagnoses. Study staff will review the medical record to confirm potential participant eligibility and to identify their linkage to an MGH primary care physician. Access to patients' medical records will be restricted to this pre-enrollment recruitment phase.
- 2) Study staff then will obtain permission for initial contact from each potentially eligible patient's PCP by having providers review letters and discard ones that they do not approve.

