### Inclusion/Exclusion Criteria

Inclusion and exclusion criteria were selected following guidelines for psychosocial treatment development and for bridging efficacy with effectiveness. Women and minorities will not be excluded. Screening will be done through patient self-report either in person (when patients are recruited from the MGH NF clinic) or via Zoom (when patients are recruited through CTF).

| Inclusion Criteria                                                    | Exclusion Criteria                                                                       |
|-----------------------------------------------------------------------|------------------------------------------------------------------------------------------|
| 1. Has a diagnosis of NF1, NF2 or schwannomatosis and is 18 or older. | 1. Has major medical comorbidity not NF related expected to worsen in the next 12 months |

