## MIND-BODY SKILLS TRAINING FOR ADULTS WITH NEUROFIBROMATOSIS

|                                                                                                                                       |                                                                                                                                                                                                                    |
|---------------------------------------------------------------------------------------------------------------------------------------|--------------------------------------------------------------------------------------------------------------------------------------------------------------------------------------------------------------------|
| 2. Is capable of completing and fully understanding the informed consent process and the study procedures and assessments in English. | 2. Recent (within past 3 months) change in antidepressant medication                                                                                                                                               |
| 3. At least a 6 th grade self-reported reading level.                                                                      | 3. Recent participation in cognitive behavioral therapy or relaxation therapy (within past 3 months)                                                                                                               |
| 4. Self reported difficulties coping with stress and NF symptoms.                                                                     | 4. Has significant mental health diagnosis requiring immediate treatment (e.g., untreated bipolar disorder, psychotic disorder, active substance dependence)- by self report and observation during pre-screening. |
| 5. Score of 6 or higher on the PSS-4.                                                                                                 | 5. Unable or unwilling to complete assessments electronically via REDCap.                                                                                                                                          |

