### *Justification for exclusion criteria:*

1. The presence of a major medical comorbidity not NF related represents an additional huge stressor, which can impact reports and confound results. In our preliminary RCT we had no patients excluded due to this criterion.
2. This exclusion criterion is used to ensure that any intervention effects are due to active ingredients of the intervention, not due to an antidepressant regimen change. In our preliminary RCT we had no patients excluded due to this criterion.
3. The 3RP-NF teaches elements of Cognitive Behavioral Therapy and Relaxation training. This exclusion criterion is meant to ensure that potential gains are due to the 3RP-NF not other interventions. In our preliminary RCT we had no patients excluded due to this criterion.
4. The presence of untreated major mental illness is also an exclusion criterion. Those presenting for

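### The three-month look-back in exclusion 3 leaves former participants of the sponsor's own 3RP-NF and HEP-NF pilots eligible, which can dilute the treatment contrast and puts blinding at some risk

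*Protocol*

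**What the plan says.** Section III, Inclusion/Exclusion Criteria, lists six exclusions. Only the third concerns earlier psychosocial treatment: "Recent participation in cognitive behavioral therapy or relaxation therapy (within past 3 months". The justification gives its purpose: "This exclusion criterion is meant to ensure that potential gains are due to the 3RP-NF not other interventions". Eligibility is established from what the patient reports: "Screening will be done through patient self-report either in person" or by Zoom.

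On recruitment, section III names the NF clinic at the sponsor's hospital and the CTF, and says of the CTF route: "We have used this method of recruitment successfully in our preliminary clinical trial". Section I shows where the two pilots found their participants. For the in-person 3RP-NF pilot (Study 3): "Patients presenting to our Neurofibromatosis Clinic who reported stress and difficulties coping to their neurologist were asked to participate in the mind-body study". For the videoconference pilot RCT (Study 5): "Patients were recruited through the CTF outreach via a flyer asking for interest in participation in a stress management study".

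On persistence, Study 5 reports that the gains over HEP-NF held at the 6-month follow-up. The Aim 1 hypothesis in section II is that "effects will be maintained at 6 and 12 months follow-ups, compared to HEP-NF".

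On blinding, section V (strategies to avoid participant unblinding) has participants told only that they will join one of two stress management groups, and asks them not to share content while the study runs. Neither that text, the eligibility criteria nor the recruitment text asks about or bars earlier enrolment in a 3RP-NF or HEP-NF study.

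**The concern.** Exclusion 3 is there so that gains can be credited to 3RP-NF as delivered in this trial. Followed as written, it admits people who have already had 3RP-NF, provided more than three months have passed. Such a person allocated to HEP-NF is a control who already has the experimental skills. Allocated to 3RP-NF, the same person repeats a programme already taken. Either way the contrast between arms shrinks.

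The rule also misses former HEP-NF participants at any interval, because section V describes HEP-NF as containing no relaxation, cognitive behavioural or positive psychology training. They carry no 3RP-NF skills, but this trial reuses the HEP-NF sessions from the pilot RCT, so they could notice whether the content is the same as before or different. The outcomes are self-reported questionnaires and the 3RP-NF groups have 5-7 members, so knowledge brought in from outside matters more than it would with an objective endpoint.

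**Working it through.** **Pool of former participants.** Study 3 gives 20 on 3RP-NF (16 completers). Study 5 gives 32 on 3RP-NF and 31 on HEP-NF.
- Exposed to 3RP-NF: 20 + 32 = 52.
- Exposed to either programme: 52 + 31 = 83, and 83/224 = 37% of the planned sample. This compares the pool with the trial size. It does not predict re-entry.

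**Look-back against reported persistence.** Table 1 of the protocol gives unadjusted pilot means for the 3RP-NF arm.
- QoL Physical: 68.53 at baseline, 76.34 at post-test and 76.34 at 6 months, a gain of 7.81 at both later times.
- QoL Psychological: 56.90, then 67.72 (gain 10.82), then 68.05 (gain 11.15).

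So the group-mean gain was undiminished at twice the look-back. In the HEP-NF arm QoL Physical was flat (60.94, 61.06, 60.17), so carry-over on that scale is mainly a matter of former 3RP-NF trainees.

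**The plan's own power figure.** Inputs from section VI, 3.1: difference 6.25, SD 14.7 (Physical) and 10.4 (Psychological), two-sided 0.025 per outcome, 5% loss. 224 x 0.95 = 212.8, so 212 analysed, 106 per arm.
- Formula: power = Phi(d / (SD x sqrt(2/106)) - 2.241).
- Physical: SE = 14.7 x sqrt(2/106) = 2.019; 6.25/2.019 = 3.095; 3.095 - 2.241 = 0.854; power = 80.3%. This reproduces the stated 80%.
- Psychological: SE = 10.4 x sqrt(2/106) = 1.429; 6.25/1.429 = 4.375; power = 98.4%, against a stated 96%. The plan's figure is on the cautious side, and the difference does not bear on this point.

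**Illustration of dilution.** Assume k of the 224 are former 3RP-NF trainees, spread evenly over the arms, with no further difference between arms among them and the SD unchanged. The expected difference is then 6.25 x (1 - k/224).

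| k | share of 224 | difference | power, Physical | power, Psychological |
|---|---|---|---|---|
| 0 | 0% | 6.25 | 80.3% | 98.4% |
| 5 | 2.2% | 6.11 | 78.4% | 97.9% |
| 10 | 4.5% | 5.97 | 76.3% | 97.4% |
| 20 | 8.9% | 5.69 | 71.8% | 95.9% |
| 52 (every former trainee) | 23.2% | 4.80 | 55.4% | 86.8% |

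The last row is an extreme bound, not an expectation. The documents give no re-entry rate, so k is an assumption throughout.

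**The case against.** The other side has several good points.

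- **Blinding.** A reader might infer that one returner is enough to unblind a whole group. The documents do not support that. Pilot RCT participants were themselves blind to which programme was experimental, satisfaction was similar in both arms, and nothing says they were told afterwards. A returner could recognise the content without knowing which arm it belongs to. Those from the open in-person pilot know 3RP-NF as a study programme, but they number at most 20. What stands is a risk: section V deals with sharing during the study and not with knowledge brought into it. Its argument that leakage is conservative concerns techniques reaching the controls. It does not cover a returner who infers his or her own allocation, and there the direction of bias is unknown.
- **Carry-over and eligibility pull against each other.** Entry requires self-reported difficulty coping and a PSS-4 score of 6 or more, so people who kept their gains are less likely to qualify, and those who lost them might benefit again. This stands. It makes zero added effect a pessimistic assumption. But the criteria bar nobody for earlier exposure.
- **Scale.** A large loss of power is easy to produce on paper. A 20% share would be 0.20 x 224, about 45 people, out of only 52 ever trained. That is not plausible, particularly as one CTF email drew 255 inquiries and only 65 people were screened in the pilot RCT.
- **No formal contradiction.** The 6-month result is a group mean and 12-month maintenance is a hypothesis under test. Neither dictates a look-back length. It remains true that a three-month window is shorter than the persistence the protocol itself reports.
- **Direction.** Randomisation balances returners on average, so carry-over pulls toward no difference. It does not create a false positive.

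**Conclusion.** The gap is real. The only prior-treatment rule is a three-month window, the trial draws on the two sources that supplied the pilots, and former participants of either programme can enter. The rule therefore falls short of its stated attribution purpose.

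The main expected consequence is dilution by returning 3RP-NF trainees. QoL Physical, planned at 80% with almost no reserve, would be at about 76% with 10 of them and about 72% with 20. QoL Psychological would remain at about 96% or more. These figures rest on an assumed number of returners and on their having no added effect, so they illustrate sensitivity and are not a forecast. Weaker blinding is possible but not shown, and inflation of the type I error through carry-over is not expected. The point merits a change because the remedy is small and eligibility has to be settled in the protocol.

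**What to change.** Add to exclusion 3: any previous participation, at any time, in a 3RP-NF or HEP-NF study. Check it at the baseline screen against the sponsor's pilot enrolment lists, not by self-report alone. Keep the three-month rule for other cognitive behavioural or relaxation therapy. If any former participants have already been enrolled, record their earlier exposure and add a sensitivity analysis without them.

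The bar should not extend to every 3RP programme. The parent programme has been used in other patient groups, and the pilot lists could not verify that exposure.

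The cost is one eligibility line, a list check, and up to about 83 known people leaving the recruitment pool. Sample size and planned power are unchanged. Section III also mentions ongoing trials of adapted 3RP-NF versions in adolescents and in deaf NF2 patients. The wording should say whether these count. Their numbers are not given, and deafened patients are already excluded from this trial under exclusion 6.
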